### Data collection and statistics

Data will be collected partially by means of a secured Internet module and partially by hard-copy datasheets. The secured online module is especially designed for the PRECious trial. Hard-copy datasheets, such as completed quality of life questionnaires will be sent to the VU medical center by mail, were they will be kept in a secured room. Data will be collected daily until discharge. PROMs will be collected preoperatively, and at 5 days, 3 months and 12 months postoperatively. A study chart for measurements is depicted in Table 1.

**Table 1 Tab1:** Study measurements

	Study period										
	Enrolment	Allocation	Post-allocation								Close-out
Time point	Pre-operative	Pre-operative	Surgery	POD 2	POD 3	POD 4	POD 5	Discharge	3 Mo	12 Mo	t_x_
Enrolment											
Eligibility screen	X										
Informed consent	X										
Allocation		X									
Interventions											
Control group		X									
CRP measurement				X	X	X	X				
QOL questionnaire		X					X		X	X	
PRECious group											
CRP measurement				X	X	X	X				
CT if CRP >140 mg/L					X	X	X				
QOL questionnaire		X					X		X		
Assessments											
Control group											
List baseline variables		X									
List operative data			X								
List admission data								X			
Quality of life		X					X		X	X	
List morbidity								X	X	X	
List survival								X	X	X	
PRECious group											
List baseline variables		X									
List operative data			X								
List admission data								X			
Quality of life		X					X		X	X	
List morbidity								X	X	X	
List survival								X	X	X	X

*POD* postoperative day, *Mo* months, *CRP* C-reactive protein, *CT* computed tomography scan, *QOL* Quality of Life, T_x_ end of protocol

One research fellow in the VU medical center will monitor the data for all included patients, and maintain regular contact with all participating centers. Due to the nature of the study the researcher cannot be blinded, hence an external monitoring committee (Clinical Research Bureau, Amsterdam, Netherlands) is installed and will assess data collection. All required parameters will be collected in an SPSS data file. Data analysis will be performed according to the intention-to-treat principle. Continuous variables will be compared using the *t* test or Mann-Whitney *U* test, as appropriate. Frequencies will be compared using the Chi-square or McNemar tests, as appropriate.

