### Endpoints

The primary endpoint of the study consists of a combined endpoint entailing all morbidity and mortality due to major complications. Complications will be classified according to a modified Clavien-Dindo classification in two groups [34, 35]. Group I consists of grade I and grade II complications, which are classified as minor. Early detection of major complications that may require invasive treatment, such as re-laparotomy or percutaneous drainage and/or intensive care admission, which might even lead to death, as classified by Clavien-Dindo grades III, IV and V, is of major importance. The comprehensive complication index will also be calculated [38]. All mortality and morbidity after major complications will be recorded, entailing fistula; bowel obstruction or herniation; abscesses; wound dehiscence; abdominal compartment syndrome; unplanned enterostomy; enterostomy dysfunction; myocardial infarction; pulmonary embolism; respiratory insufficiency; urosepsis; cerebrovascular accident; bleeding, and anastomotic leak.

Secondary endpoints will be patient-related outcome measures (PROMs), measured with the EuroQol-5D (EQ-5D) and gastrointestinal quality of life index (GIQLI) questionnaires. Furthermore postoperative recovery data will be collected in both groups, such as length of hospital stay and intensive care length of stay. Alongside the trial a cost-effectiveness analysis will be conducted.

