### Power of the study

Based on retrospective data of 399 patients who underwent MAS, we assessed all mortality and morbidity due to major complications (multiple reoperations, multiple percutaneous drainages, enterostomy during re-intervention) and found this to be 17 %. Based on the results of den Dulk, who report a decrease in mortality following implementation of a clinical item scoring list, we calculated the following sample size [6]: a group sample size of 525 in group 1 and 525 in group 2 to achieve 80 % power to detect a difference in frequency of morbidity in the control group, which is 17 %, in comparison to the PRECious group, with an expected morbidity of 11 %. The test statistic used is the two-sided Mantel-Haenszel test. The significance level of the test was targeted at 0.05.

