### Patient allocation and design

Patients will be informed about the study at the outpatient clinic. The patient will be included upon admission after informed consent has been obtained. Due to the nature of the study, a parallel-randomized design is not the preferred option, because this would allow for bias by crossover and automated CRP and CT enquiries by physicians in both patient groups. A cluster design is not deemed feasible due to differences between the participating centers (i.e., academic and teaching hospitals). A stepped-wedge design is deemed appropriate. Due to the large number of participating centers, little bias is expected from other changes in treatment. Changes will be monitored and corrected for if applicable. Thus, the two groups will be compared according to two periods. Patients allocated to the first period will receive standard on-demand additional examinations. After a transition phase of one month allowing for implementation, all patients will be allocated to the intervention arm and will receive standardized postoperative monitoring of serum CRP levels on POD 3, 4 and 5. If CRP levels exceed 140 mg/L additional CT will be conducted.

Data collection will be via an online module, which allows for inclusion and data collection. Participating surgeons will be able to log in to the secured module via the PRECious trial website. After completing the inclusion form, an immediate response with a code number and type of postoperative control protocol will be obtained.

The nature of the study does not allow for blinding, because it would not be ethical to perform sham venous puncture, and the protocol will be known by the attending physician to allow CT to be arranged. Instead of blinding, the add-on value of CRP measurements will be tested. The attending physician will have to grade the patient in the morning before CRP levels are known, grade 1 indicating a healthy patient, grade 10 a patient at acute risk of death. The physician will also have to state whether he/she would perform CT prior to CRP levels being measured, allowing for assessment of the add-on value of the presented standardized quality control algorithm.

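### The only test stated for continuous outcomes ignores the scheduled preoperative EQ-5D and GIQLI scores, although the groups are formed by period

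*Protocol article*

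**What the plan says.** The Endpoints section makes patient-reported outcomes secondary endpoints, "measured with the EuroQol-5D (EQ-5D) and gastrointestinal quality of life index (GIQLI) questionnaires". Under Data collection and statistics the schedule is "PROMs will be collected preoperatively, and at 5 days, 3 months and 12 months postoperatively". The same section gives the only method for continuous data: "Continuous variables will be compared using the" t test or the Mann-Whitney U test, whichever suits. It names no covariate, change score or repeated-measures model, and no separate method for the questionnaires.

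On how the groups arise, Patient allocation and design says "Thus, the two groups will be compared according to two periods". Just before that, after a remark that little bias is expected from other changes in treatment, it adds "Changes will be monitored and corrected for if applicable". No method of correction is given and baseline scores are not mentioned.

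Table 1 is inconsistent on the last visit. In the PRECious group, the questionnaire row under Interventions has no mark at 12 months, while the quality-of-life row under Assessments has one. In the control group both rows have it.

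**The concern.** A preoperative score is usually a strong predictor of the same score later, and here it is scheduled before any CRP-directed care begins, so it is a legitimate covariate. A two-sample test on follow-up scores does not use it.

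In an individually randomised trial that would cost mainly precision. Here patients enter one group or the other according to when they have surgery, so randomisation does not make mean preoperative scores equal in expectation. The article itself points to differences between the participating centres when it rejects a cluster design. If the mix of hospitals or patients shifts between periods, baseline quality of life may shift too, and part of that shift would be read as an effect of PRECious.

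At stake are the quality-of-life comparisons, both their precision and their protection against a measurable baseline difference.

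**Working it through.** **The plan's own figure.** The only sample-size statement is for the binary primary endpoint: "a group sample size of 525 in group 1 and 525 in group 2 to achieve 80 % power" for 17% versus 11%, two-sided 5%. With pooled variance and no continuity correction:

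n = [1.960·√(2·0.14·0.86) + 0.842·√(0.17·0.83 + 0.11·0.89)]² / 0.06² = 524 per group, and 525 gives 80.1% power.

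The figure reproduces. It says nothing about the questionnaires, for which the article states no target difference, standard deviation or correlation. Below, 525 serves only as the group size.

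**Inputs.** From the article: 525 per group and a two-sample test with no covariate. Assumed: within-group correlation r between preoperative and follow-up score of 0.3, 0.5 or 0.7; equal standard deviations (SD) at both times; independent patients; and, for the bias rows, a systematic difference b = 0.1 SD in mean preoperative score between periods.

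**Formulas**, relative to a t test on follow-up scores:
- Standard error ratio with baseline adjustment: √(1 − r²). Equivalent increase in patients: 1/(1 − r²).
- Detectable difference at 80% power, unadjusted: (1.960 + 0.842)·√(2/525) = 0.173 SD. Adjusted: 0.173·√(1 − r²).
- Variance ratio for a change-score t test: 2(1 − r).
- Bias from a baseline shift b that carries forward with slope r: r·b for follow-up scores, (r − 1)·b for change scores, none for the adjusted comparison.
- Actual type I error of the unadjusted test: 1 − Φ(1.96 − δ) + Φ(−1.96 − δ), with δ = r·b/√(2/525) and √(2/525) = 0.0617.

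| Quantity | r = 0.3 | r = 0.5 | r = 0.7 |
|---|---|---|---|
| Standard error ratio, adjusted | 0.954 | 0.866 | 0.714 |
| Reduction in standard error | 5% | 13% | 29% |
| Equivalent increase in patients | 10% | 33% | 96% |
| Detectable difference, adjusted (unadjusted 0.173 SD) | 0.165 | 0.150 | 0.123 |
| Variance ratio, adjusted | 0.91 | 0.75 | 0.51 |
| Variance ratio, change score | 1.4 | 1.0 | 0.6 |
| Bias, unadjusted, b = 0.1 SD | 0.03 | 0.05 | 0.07 |
| Bias, change score, b = 0.1 SD | −0.07 | −0.05 | −0.03 |
| Type I error, unadjusted, b = 0.1 SD (nominal 5%) | 7.7% | 12.8% | 20.5% |

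If only 420 per group (80% of 525) returned questionnaires, the detectable difference would go from 0.193 SD unadjusted to 0.184 / 0.167 / 0.138 SD adjusted. The relative gain is the same.

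The type I error row concerns a systematic shift. A purely chance baseline difference is already within the t test's standard error; adjustment then improves precision rather than correcting bias.

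**The case against.** The strongest reply is that the sentence on continuous variables is generic. It names no questionnaire, visit or contrast, and it sits in a condensed article; a fuller protocol exists and is not shown. That lowers certainty about what will be done. It does not remove the point, because an unadjusted test is stated, these scores are continuous, and nothing else is offered for them.

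A reader might infer that baseline is certain to be ignored. The text does not go that far: a t test on change from the preoperative score would fit the sentence. It would still be less precise than ANCOVA at every r in the table, and less precise than the plain follow-up test when r is below 0.5. It would also over-correct wherever a baseline difference carries forward only in part.

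A reader might also infer that testing each visit separately drops patients with partial follow-up. That is not supported. The article does not prescribe testing by visit, and such a test would use everyone observed at that visit. Nor can it be said that every patient has a baseline score; the scores are planned, and questionnaires are sent in on paper.

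Finally, lower precision does not make an unadjusted test invalid, and the correlations are assumptions. Both objections stand. The case therefore rests on the non-randomised grouping together with a gain that is almost free.

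**Conclusion.** The point holds as an improvement to make to the secondary analyses. The stated test suits these data poorly: it names no use of a scheduled baseline score in a comparison where individual randomisation does not balance that score. The gain in standard error is about 5% to 29% for r from 0.3 to 0.7. It may be smaller at day 5, when scores shortly after major surgery may relate less to preoperative status. The bias figures depend further on an assumed 0.1 SD shift, which the article neither reports nor rules out.

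It would be too strong to conclude that baseline adjustment makes the period comparison sound. It removes only the imbalance carried by the measured score. Secular change, clustering by hospital and other case-mix differences remain. The sentence on monitoring and correcting for changes does not fill the gap, since it follows a remark about treatment and gives no method. The primary endpoint and its sample size are not affected.

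**What to change.** Replace the two-sample test for EQ-5D and GIQLI with a linear mixed model of the follow-up scores. Include the preoperative score as covariate and terms for treatment, visit, treatment-by-visit and hospital. An ANCOVA at each visit with the preoperative score and hospital is an acceptable simpler choice. Report the adjusted mean difference with its 95% CI at each visit.

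Add calendar time only if hospitals cross over at different dates. The sections on patient allocation and on the standard and PRECious groups describe a first and a second period without establishing staggered crossover. If all hospitals switch together, calendar period cannot be separated from treatment.

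Reconcile the two Table 1 rows on the 12-month PRECious questionnaire, because the 12-month contrast needs scores from both groups.

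The cost is a few sentences of analysis text and slight extra programming. The baseline adjustment needs no data beyond those already scheduled. The Trial status section says recruitment had not begun, so at that point the change could still have been prespecified.

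### The Chi-square test named for the primary endpoint has no hospital or period term, so its type I error is not protected in a period-based comparison across seven differing hospitals

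*Protocol article*

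**What the plan says.** All references are to the protocol article.

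- *Data collection and statistics* gives the only rule for comparing frequencies: "Frequencies will be compared using the Chi-square or McNemar tests, as appropriate". It mentions no stratification by hospital and no term for time.
- *Endpoints* and *Power of the study* treat the primary outcome as a frequency, 17% under control against 11% under the PRECious protocol, so that rule covers it.
- *Power of the study* plans "a group sample size of 525 in group 1 and 525 in group 2 to achieve 80 % power" and adds: "The test statistic used is the two-sided Mantel-Haenszel test". It states no strata, intracluster correlation (ICC) or period effect.
- *Patient allocation and design* says "A cluster design is not deemed feasible due to differences between the participating centers" and then adopts a stepped wedge in which the groups are two periods separated by a one-month transition. On other changes over time it says: "Changes will be monitored and corrected for if applicable".
- *Participating surgeons and clinics* lists seven hospitals, one academic and six teaching. It notes that complication rates depend on learning curves, which could affect the primary outcome.

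**The concern.** The article recognises two sources of variation, differences between hospitals and changes over time, and then names a test that uses neither. Three mechanisms can distort the crude two-by-two comparison:

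1. **Hospital-by-period variation.** If a hospital's underlying event rate drifts between periods, its patients within a period are correlated. The Chi-square standard error is then too small.
2. **Secular trend.** The intervention follows the control period, so a fall in event rate shared by all hospitals appears as benefit.
3. **Hospital imbalance, if crossover is staggered.** Hospitals that switch early supply mostly intervention patients and those that switch late mostly controls, so differences between hospitals enter the comparison.

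At stake is a claim of benefit at a nominal 5% level whose real false-positive rate may be a multiple of that.

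**Working it through.** **Inputs from the article:** 17% vs 11%, two-sided alpha 0.05, 80% power, 525 per group, seven hospitals, so 1,050/7 = 150 patients per hospital. **Assumptions (not in the article):** equal hospital sizes, ICC 0.01-0.05, cluster autocorrelation (CAC) 0.8 or 1, and the size of any trend.

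**Step 1. The plan's own sample size.** The ordinary two-proportion formula with pooled variance and no continuity correction gives

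n = [1.96·√(2·0.14·0.86) + 0.8416·√(0.17·0.83 + 0.11·0.89)]² / 0.06² = 523.8, so 524 per group.

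The stated 525 is reproduced (power 80.1%). It contains no visible allowance for hospital or period.

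**Step 2. Single switch, 75 + 75 patients per hospital, no trend, no effect.** Constant hospital effects cancel. The true variance relative to the Chi-square variance is

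inflation = 75·ICC·(1 − CAC) + (1 − ICC), and type I error = 2·[1 − Φ(1.96/√inflation)].

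| ICC | CAC | Inflation | Type I error, formula | Type I error, simulated |
|---|---|---|---|---|
| 0.01 | 0.8 | 1.14 | 6.6% | 6.8% |
| 0.02 | 0.8 | 1.28 | 8.3% | not run |
| 0.03 | 0.8 | 1.42 | 10.0% | 10.6% |
| 0.05 | 0.8 | 1.70 | 13.3% | 13.0% |
| 0.01-0.05 | 1 | 0.99-0.95 | 4.9-4.4% | 4.9-4.6% |

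The simulation used 20,000 trials per setting. The last row is the favourable case: balanced hospitals, constant effects and no trend give a nominal or slightly conservative test.

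**Step 3. Single switch, ICC 0, a shared fall in event rate and no treatment effect.** For a 3-point fall (17% to 14%):

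- pooled SE = √(2·0.155·0.845/525) = 0.02234
- unpooled SE = √((0.17·0.83 + 0.14·0.86)/525) = 0.02232
- P(reject) = 1 − Φ((1.96·0.02234 − 0.03)/0.02232) + lower tail of about 0.0005 = 26.9%.

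Falls of 1 and 2 points give 7.2% and 14.3%. Stratifying by hospital does not help: a hospital-stratified Mantel-Haenszel test gives 26.6% at 3 points (simulated).

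**Step 4. Hypothetical stagger: one hospital crossing per step, eight periods of 150/8 = 18.75 patients per hospital, CAC 1, no trend.** Intervention minus control counts per hospital are 18.75 × (−6, −4, −2, 0, 2, 4, 6), and these seven multipliers have sum of squares 112. Hence

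inflation = (1 − ICC) + ICC·[(18.75/525)²·112]/(2/525) = (1 − ICC) + 37.5·ICC.

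| ICC | Inflation | Type I error, formula | Type I error, simulated |
|---|---|---|---|
| 0.01 | 1.365 | 9.3% | 9.5% |
| 0.03 | 2.095 | 17.6% | 17.8% |
| 0.05 | 2.825 | 24.4% | 23.7% |

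Here a hospital-stratified Mantel-Haenszel test holds 4.6-5.2%. It fails once a trend is added: with a 6-point fall over the trial and ICC 0 it gives 27.7%, against 21.6% for Chi-square.

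**Step 5. Power if the variance is allowed for (single switch, CAC 0.8, ICC 0.02).** With both variances multiplied by 1.28, power = Φ((0.06 − 1.96·√(0.2408·1.28/525))/√(0.2390·1.28/525)) = Φ(0.518) = 70%, before any small-sample correction, which lowers it further. Here 0.2408 = 2·0.14·0.86 and 0.2390 = 0.17·0.83 + 0.11·0.89.

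**The case against.** **The layout may not be staggered.** The text describes two periods: everyone under control first, then everyone under the intervention. It states no number of steps and no order of hospitals, and the flow chart is not shown. This stands. The staggered figures are hypothetical, and under a common switch a model with period effects could not separate them from treatment.

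**A reader might infer that the primary p-value is simply invalid.** The article does not support that. In the balanced, constant, trend-free case the crude test holds its level. The inflation depends on ICC, CAC and trend values that the article does not give.

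**A reader might infer that a paired test is planned for unpaired groups.** McNemar is listed for frequencies in general, where appropriate. The article also has physicians record, before CRP is known, whether they would order CT. That is a within-patient question for which a paired test can be suitable. Naming McNemar is not an error, although its use could be stated.

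**A reader might infer that the Mantel-Haenszel label undermines the sample size.** It does not. Without strata, that statistic is Pearson's Chi-square times (N − 1)/N = 1049/1050, and the stated N is reproduced. The difference is one of wording.

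**Time is not wholly ignored, and an article condenses.** The article does promise correction of changes where applicable. But the promise is conditional and gives no method, and neither named test can carry it out. The expectation of little bias rests on the number of centres, and adding centres does not remove a trend they share. A fuller document may hold a model, but this article does not merely leave the test open: it names one that does not fit its design.

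**Conclusion.** The concern holds in this form: the Chi-square test named for frequencies, and hence for the primary endpoint, leaves type I error unprotected against three features that the design makes plausible.

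- **Hospital-by-period variation:** about 7-13% under a single switch with assumed ICC 0.01-0.05 and CAC 0.8.
- **Secular trend:** about 27% for an assumed shared fall of 3 points, which is half the 6-point target difference.
- **Hospital imbalance, only if crossover is staggered:** about 10-24% for assumed ICC 0.01-0.05.

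It is near nominal only when hospitals are balanced, their effects are constant and there is no trend. The article gives reason to doubt the second and third conditions. The planned 525 per group is arithmetically correct for independent patients and is not itself in dispute here.

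**What to change.** State whether the hospitals switch together or at different times. Then replace the crude test for the primary endpoint with one pre-specified model, and name that same analysis in *Power of the study*.

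- **Different times:** mixed-effects logistic regression with treatment, fixed calendar-period effects, random hospital and hospital-by-period effects, and a small-sample correction for seven clusters.
- **All together:** period effects cannot be identified. Use a hospital-adjusted analysis that allows for hospital-by-period variation with a small-sample correction, and adjust for procedure type and ASA class. State plainly that this is a before-after comparison that cannot be separated from a shared time trend.

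As wording notes, say that McNemar serves only the within-patient comparison of CT decisions, and remove the difference between Mantel-Haenszel and Chi-square.

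**Cost:** slightly more analysis work, a wider interval and power below 80%, for example about 70% before small-sample correction at ICC 0.02 and CAC 0.8 under a single switch. The article reports that recruitment has not begun, so the text can still be changed before data exist. No choice of model removes the time confounding if all hospitals switch together.
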